### **7.3. Lost to Follow up**

A participant will be considered lost to follow-up if he or she repeatedly fails to return for scheduled visits and is unable to be contacted by the study site.

The following actions must be taken if a participant fails to return to the clinic for a required study visit:

- The site must attempt to contact the participant and reschedule the missed visit as soon as possible and counsel the participant on the importance of maintaining the assigned visit

schedule and ascertain whether or not the participant wishes to and/or should continue in the study.

- Before a participant is deemed lost to follow up, the investigator or designee must make every effort to regain contact with the participant (where possible, telephone calls and, if necessary, a certified letter to the participant's last known mailing address or local equivalent methods). These contact attempts should be documented in the participant's medical record.
- Should the participant continue to be unreachable, he/she will be considered to have withdrawn from the study.

## **8. Study Assessments and Procedures**

- Study procedures and their timing are summarized in the SoA. Protocol waivers or exemptions are not allowed.
- Immediate safety concerns should be discussed with the sponsor immediately upon occurrence or awareness to determine if the participant should continue or discontinue study intervention.
- Adherence to the study design requirements, including those specified in the SoA, is essential and required for study conduct.
- All screening evaluations must be completed and reviewed to confirm that potential participants meet all eligibility criteria. The investigator will maintain a screening log to record details of all participants screened and to confirm eligibility or record reasons for screening failure, as applicable.
- Procedures conducted as part of the participant's routine clinical management (e.g., blood count) and obtained before signing of the ICF may be utilized for screening or baseline purposes provided the procedures met the protocol-specified criteria and were performed within the time frame defined in the SoA.
- Safety or laboratory results that could unblind the study will not be reported to blinded personnel until the study has been unblinded.
- Repeat or unscheduled samples may be taken for safety reasons or for technical issues with the samples.

### **8.1. Assessments**

Planned time points for all primary and secondary assessments are provided in the SoA.

#### **8.1.1. Visit Assessments**

##### **Screening Visit**

Participants will receive the information relative to proceedings and study visits. If they agree to participate, written informed consent would be signed before any procedure. Screening assessments include: thorough medical history and complete physical exam, review of inclusion and exclusion criteria and laboratory assessment (Hematology, creatinine, eGFR, ALT, AST, fasting lipids, fasting glucose, HOMA-IR, Glycated hemoglobin (Hb A1c), CD4+ CD8+ cell count, HIV-1 RNA, FSH).

##### **Visit 1 (Baseline)**

Review of inclusion and exclusion criteria, concomitant medication, physical exam including anthropometric measurements (weight, height, waist circumference, blood pressure, and heart

rate), dispense study drug (metformin 850 mg once daily), dispense healthy lifestyle information, concomitant medication review, laboratory assessments (HOMA-IR, whole blood sample for epigenetic age acceleration measurements and leucocyte telomere length, lymphocyte and monocyte subpopulations, Inflammatory and procoagulant biomarkers, Blood TAME markers, oxidative stress and DNA damage markers), Frailty assessments (Fried index, grip strength, walking speed, short physical performance battery [SPPB]) and geriatric scales (mini-nutritional assessment and modified Rockwood Clinical Frailty Scale).

### **Visit 2 (Week 4 $\pm$ 2 days)**

Concomitant medication, adverse events, adherence, symptom guided physical exam, limited safety laboratory panel (Hematology, renal and liver function, fasting glucose, urine), study drug titration (metformin placebo 850 mg twice daily) except those on dolutegravir based regimen.

### **Visit 3 (Week 8 $\pm$ 2 days)**

This visit will be performed only in patients in whom the dose of metformin has been increased to 850mg dose twice daily in week 4.

Concomitant medication, adverse events, adherence, symptom guided physical exam, limited safety laboratory panel (Hematology, renal and liver function, fasting glucose, urine).

### **Visits 4, 6, 8 (Week 24 $\pm$ 7 days, week 72 $\pm$ 7 days, and week 120 $\pm$ 7 days)**

Concomitant medication, adverse events, adherence, symptom guided physical exam, full safety laboratory panel (Hematology, renal and liver function, fasting glucose, fasting lipids, proteins, albumin, vitamin D, CD4+ cell count, HIV-1 RNA, urine).

### **Visits 5, 7, 9 (Week 48 $\pm$ 7 days, week 96 $\pm$ 7 days, and week 144 $\pm$ 7 days)**

Concomitant medication, adverse events, adherence, symptom guided physical exam, anthropometric measurements (weight, height, waist circumference, blood pressure, and heart rate), laboratory assessments (full safety laboratory panel, Hematology, renal and liver function, fasting glucose, fasting lipids, proteins, albumin, vitamin D, CD4+ and CD8+ cell count, HIV-1 RNA, urine, HOMA and HbA1c, whole blood sample for epigenetic age acceleration measurements and leucocyte telomere length, immune profile, inflammatory and pro-coagulant biomarkers, blood TAME markers, oxidative stress and DNA damage markers). Frailty testing: Fried index, grip strength, walking speed, short physical performance battery (SPPB) and geriatric scales (mini-nutritional assessment and modified Rockwood Clinical Frailty Scale).

### **Early discontinuation visit**

At the time of discontinuing from the study, if possible, an early discontinuation visit should be conducted, as shown in the SoA. See SoA for data to be collected at the time of study discontinuation and follow-up and for any further evaluations that need to be completed (at least detail the participant's evolution, date of treatment discontinuation, and new prescribed therapy).

## **8.2. Safety Assessments**

Planned time points for all safety assessments are provided in the SoA.

### **8.2.1. Physical Examinations**

- A complete physical examination will include, at a minimum, assessments of the Cardiovascular, Respiratory, Gastrointestinal and Neurological systems. Height and weight will also be measured and recorded.
- A brief physical examination will include, at a minimum, assessments of the skin, lungs, cardiovascular system, and abdomen (liver and spleen).
- Investigators should pay special attention to clinical signs related to previous serious illnesses.

### **8.2.2. Vital Signs**

- Pulse rate, respiratory rate, blood pressure, height and weight will be assessed.
- Blood pressure and pulse measurements will be assessed with a completely automated device. Manual techniques will be used only if an automated device is not available.

Blood pressure and pulse measurements should be preceded by at least 5 minutes of rest for the participant in a quiet setting without distractions (e.g., television, cell phones) and before blood collection for laboratory tests.

### **8.2.3. Clinical Safety Laboratory Assessments**

- See Appendix 2 for the list of clinical laboratory tests to be performed and to the SoA (Section 1.3) for the timing and frequency.
- The investigator must review the laboratory report, document this review, and record any clinically significant changes occurring during the study as an AE. The laboratory reports must be filed with the source documents.
- Abnormal laboratory findings associated with the underlying disease are not considered clinically significant unless judged by the investigator to be more severe than expected for the participant's condition.
- All laboratory tests with values considered clinically significantly abnormal during participation in the study should be repeated until the values return to normal or baseline or are no longer considered clinically significant by the investigator or medical monitor.

- If clinically significant values do not return to normal/baseline within a period of time judged reasonable by the investigator, the etiology should be identified, and the sponsor notified.
- All protocol-required laboratory tests, as defined in Appendix 2, must be conducted in accordance with the laboratory manual and the SoA (Section 1.3).
- If laboratory values from non-protocol specified laboratory tests performed at the institution's local laboratory require a change in participant management or are considered clinically significant by the investigator (e.g., SAE or AE or dose modification), then the results must be recorded.

### 8.3. Other study laboratory assessments

- Collection of biological samples for biomarker research is also part of this study. Blood samples for biomarker research are required and will be collected from all participants in this study as specified in the SoA.
- Samples will be tested for protocol-specific endpoints to evaluate their association with the study intervention.
- These blood laboratory assessments will include (See SoA and Appendix 2 for further information).
  - Laboratory tests for epigenetic age acceleration by DNA methylation arrays: Determination of epigenetic age acceleration according to four epigenetic clocks (Horvath's clock, Hannum's clock, PhenoAge and GrimAge).
  - Telomere length in PBMC. Genomic DNA from frozen PBMCs would be performed using the QIAamp DNA Blood Kit Mini Kit (Qiagen, Germany). Relative telomere length, expressed as ratio of telomere (T) to single-copy gene (S), would be determined by monochrome quantitative multiplex polymerase chain reaction (qPCR) assay, with minor modifications as described in our prior study(38) . Baseline and follow-up samples would be assayed in triplicate on the same PCR plate and those with a coefficient of variation (CV) greater than 10% would be reanalyzed.
  - Immunophenotype by flow cytometry. Fresh PBMCs appropriately stained would be acquired with a Beckman Coulter Navios cytometer and/or with a Celesta BD cytometer to quantify different lymphocyte subsets. Analysis of collected data would be performed with Flowlogic software. Flow Cytometry in fresh blood samples will analyse haematopoietic progenitors (CD34), Lymphocyte T (CD3+ CD4+ and CD8+ [RTE (CD45RA, CD31), naïve (CD27+, CD45RA+), central memory (CD27+, CD45RA), effector memory (CD27CD45RA), TEMRA (CD27, CD45RA+), Activated (CD38+, HLA DR+), senescent cells (CD28CD57+), exhaust (PD1+)], Lymphocyte B (CD19+) [(naïve (CD27, IgD+), class-switched memory (CD27+, IgD), non class-switched memory (CD27+, IgD+)], Natural killer (CD56dim CD16hi, CD56hi CD16-/low), T-regs (CD25+, FoxP3+), monocyte subpopulations (classic CD14++ CD16, non-classic CD14++ CD16++, intermediate CD14+ CD16+).

- Blood TAME biomarkers (39) and other inflammatory and pro-coagulant biomarkers: IL-1 beta, TNF-alfa, D-dimer, IL-6, TNF $\alpha$  receptor, C-Reactive Protein, GDF15, IGF-1 C-Reactive Protein, Fasting insulin, Cystatin C, NT-proBNP. Cytokines and soluble markers would be determined in serum by solid phase ELISA quantikine human immunoassay (R&D system, Minnesota, USA). Baseline and follow-up samples would be assayed in duplicate on the same plate.
- DNA damage analysis by H2AX histone levels measurement: Nuclear protein extraction from frozen PBMCs would be performed using the CellLytic™ NuCLEAR™ Extraction Kit (Merck, Darmstadt, Germany).  $\gamma$ H2AX levels would be determined by Western blot using Phospho-Histone H2A.X-P-Ser139 antibody 1:1000 (Cell Signaling Technology, Danvers, MA, USA) Blots would be washed and re-incubated with an Actin antibody 1:200 (Sigma-Aldrich, St. Louis, MI, USA), as loading control. Anti-rabbit IgG-HRP 1:2000 (Santa Cruz Biotechnology, Dallas, TX, USA) would be used as secondary antibody. Blots would be incubated with the Western Blotting Luminol Reagent (Santa Cruz Biotechnology Dallas, TX, USA). Protein levels would be analyzed with ImageJ. Baseline and follow-up samples would be assayed in duplicate on the same blot and repeated twice.
- Catalase, SOD1 and SOD2 levels: Total RNA would be obtained from frozen PBMCs. cDNAs would be generated from 2  $\mu$ g of RNA and qPCR would be performed by triplicate using specific Taqman probes. Actin would be amplified as loading control. Relative gene expression quantification would be calculated according to the comparative threshold cycle method ( $2^{-\Delta\Delta Ct}$ ) and normalized to the amplification signal obtained for PBMCs for each mRNA. Baseline and follow-up samples would be assayed on the same plate.
- ROS levels: One million of thawed PBMCs, previously cryopreserved, would be exposed to TBHP (tert-butyl hydroperoxide) as positive control or to N-acetylcystein as negative control or in absence (proper ROS levels). ROS levels would be determined using CellROX Green reagents (ThermoFisher, Massachusetts, USA) and analyzed by flow cytometry. Baseline and follow-up samples would be assayed twice.
- Viral reservoir in PBMC and CD4 T-cell. Genomic DNA from frozen PBMCs and CD4 T-cells ( $1 \times 10^6$  cells and  $5 \times 10^6$  cells) would be performed using the QIAamp DNA Blood Kit Mini Kit (Qiagen, Germany).

To measure total and integrated (Gag) HIV-1 DNA, nucleic acid would be quantified by nested real time PCR. All measurements were performed in triplicate. The first PCR would be performed by using primers to the human Alu and HIV-gag regions. The second PCR, real-time PCR, detects HIV-specific products by using primers to the R and U5 regions within the HIV long terminal repeat (LTR) and a specific fluorescent probe. In the case of integrated HIV DNA, the Alu primer serves as an anchor in the human genome and the gag primer serves as an anchor in the HIV genome. Binding sites for these two primers would be present in the DNA target template only when HIV has integrated into the human genome. Furthermore, when the primer binding sites are close enough and aligned correctly, the region between them can be amplified exponentially. Quantification would be achieved by

comparing the resultant signals to those obtained with an integration standard: ACH2 cells carrying one copy of integrated HIV-DNA per cell (NIH AIDS Reagent Program). To measure the background signal or the signal expected from unintegrated DNA, a control reaction using only the gag primer would be included in the first PCR. The signals from Alu-gag and gag-only would be compared to make sure the Alu-gag signal is stronger, and thus that the sample is positive for integration. Then a correlation would be developed that relates the PCR signals to proviral level, which is used to quantify the level of integration in the samples. To normalize the number of cells per sample, we would use a specific couple of primers and a fluorescent probe in a real-time PCR for CD3 amplification.

To measure CA US HIV-RNA, total RNA would be isolate from total CD4 + T-cells using RNeasy Mini Kit with on-column DNase treatment (Qiagen), according to the manufacturer's instructions. The quality (260nm/280nm ratio) and quantity of RNA collected were evaluated by spectrophotometry on a Nanodrop instrument. Extracted cellular RNA would be treated with DNase (DNA-free kit; Thermo Fisher Scientific, Waltham, MA) to remove DNA that could interfere with quantitation and reverse transcribed using random primers and SuperScript III reverse transcriptase (Thermo Fisher Scientific). CA HIV-1 US RNA would be measured using seminested quantitative PCR (qPCR)-based assays. Retrotranscription would be performed with random hexamers as primers and SuperCript III (Invitrogen, Waltham, MA) according to the manufacturer's instructions. Quantification of LTR-Gag HIV-RNA would be performed by using specific external primers for the first amplification and internal primers for the second amplification; and a fluorescent probe. US LTR-gag HIV-RNA standards were generated from plasmids by in vitro transcription (MEGAscript™ T7 Transcription Kit, ThermoFisher). The number of copies of each transcript was normalized to the levels of the reference gene beta glucuronidase (GUSB). All measurements were performed in triplicate.

To measure Intact proviral DNA assay (IPDA) genomic DNA would be extracted using the QIAamp DNA Mini Kit (Qiagen). DNA concentrations would be determined using a Nanodrop instrument. Quantification of intact, 5' deleted, and 3' deleted and/or hypermutated proviruses would be carried out using specific primer/probe combinations optimized for subtype B HIV-1 using the technique described by Bruner K et al (26) using droplet digital PCR. All measurements would be performed in triplicate.

- Peripheral Blood Mononuclear Cells (PBMCs) would be isolated by differential density gradient centrifugation from whole blood by exploiting differences in cell density. Granulocytes and erythrocytes have a higher density than mononuclear cells and therefore sediment during centrifugation. The PBMCs would be used freshly to determine the immunophenotype. The PBMC destined to telomere length measurement, DNA damage evaluation and catalase, SOD1, SOD2 mRNA expression levels would be frozen. To determine reactive oxygen species PBMCs would be cryopreserved.

- CD4 T-cell isolation from fresh PBMCs using the CD4 T cell isolation Kit, Human (Miltenyi, Alemania) by negative selection. Purity of CD4 T-cell isolation would be evaluate by flow cytometry. Samples would be stored at -80°C.

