| 
 
To evaluate the effect of metformin compared to placebo as assessed by the increase in immune profile recovery at week 48, 96 and 144
 
                                                                                                                           | 
 
Immune profile: % and absolute number of CD4+ T cells, CD8+ T cells, CD4+/CD8+ ratio, haematopoietic progenitors, CD4+ and CD8+ T-cell subsets (recent thymic emigrants, naïve, central and effector memory, TEMRA, activated, exhausted and senescent), T-reg, B-cell subsets (naïve, class-switched memory, non-class switched memory), NK subsets (CD56dim CD16hi, CD56hi CD16-/low) and monocytes (classic, non-classic and intermediate)
 
 |
| 
 
To evaluate the effect of metformin compared to placebo as assessed by the reduction of inflammatory biomarkers' changes at week 48, 96 and 144
 
                                                                                                                 | 
 
Changes in the inflammatory markers: IL-6, CRP, D-Dimer
 
                                                                                                                                                                                                                                                                                                                                                                                                                                                         |

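### The printed monocyte definitions appear to exchange the CD14 levels of the intermediate and non-classic subsets, so as written two components of the secondary immune-profile endpoint would not match their names

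*Protocol*

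**What the plan says.** Protocol section 3 (and the synopsis, section 1.1) lists "monocytes (classic, non-classic and intermediate" among the cell populations of the secondary immune-profile endpoint, which is assessed at weeks 48, 96 and 144.

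Section 8.3, under immunophenotyping by flow cytometry, defines the subsets by surface markers. The first is "classic CD14 ++ CD16", followed by a minus sign. The other two are "non-classic CD14 ++ CD16 ++ , intermediate CD14 + CD16", followed by a plus sign. Table 3 in section 10.2 repeats the same three definitions.

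The protocol gives no fluorescence cut-offs, cites no nomenclature for the monocyte names, does not say whether one plus and two pluses are separate levels, and has no rule for monocytes outside the three definitions. Section 8.2.3 says that the tests defined in Appendix 2 "must be conducted in accordance with the laboratory manual and the SoA". The laboratory manual is not among the documents.

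**The concern.** The name intermediate implies a place between classic and non-classic. The printed definition has that place on CD16 but not on CD14, where it sits below both other subsets. In ordinary flow-cytometry usage, intermediate monocytes keep the high CD14 of classic cells and gain CD16, while non-classic monocytes have reduced CD14 and the highest CD16. The printed definitions give the reverse on CD14.

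This is a rule the protocol states, not a detail it leaves to a later document. A laboratory that followed it would report values under the names intermediate and non-classic that do not belong to those cells. An effect of metformin on either subset could then be lost, or, on one reading of the symbols, be mixed into the other subset's result.

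**Working it through.** There is no stated figure to reproduce. The check is a comparison of the definitions, followed by an enumeration.

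**Inputs** (sections 8.3 and 10.2, Table 3, which agree): classic CD14++CD16-; intermediate CD14+CD16+; non-classic CD14++CD16++.

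**Step 1: order along each marker**, from classic through intermediate to non-classic.

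- CD16 as printed: -, +, ++. This is ordered.
- CD14 as printed: ++, +, ++. This is not ordered; intermediate is the lowest, and non-classic equals classic.
- CD14 with the symbols of intermediate and non-classic exchanged: ++, ++, +. This is ordered, and CD16 is unchanged.

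Exchanging the two names instead would give CD14 as ++, ++, + but CD16 as -, ++, +, so it repairs one marker and breaks the other. Exchanging the CD14 symbols of classic and intermediate (+, ++, ++) would also restore order, but it would make classic cells the low-CD14 subset, contrary to ordinary usage. Order alone therefore shows that something is wrong. Choosing the first exchange also relies on the ordinary meaning of the names.

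**Step 2: where each kind of cell is counted.** The symbols allow 2 CD14 levels by 3 CD16 levels, so 2 x 3 = 6 combinations. Each is assigned under two readings: one plus and two pluses as distinct levels, or one plus as at least that level.

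| Cell | Printed, distinct levels | Printed, at least + | Exchanged, distinct levels | Exchanged, at least + |
|---|---|---|---|---|
| CD14++CD16- | classic | classic | classic | classic |
| CD14++CD16+ | none | intermediate | intermediate | intermediate |
| CD14++CD16++ | non-classic | non-classic and intermediate | none | non-classic and intermediate |
| CD14+CD16- | none | none | none | none |
| CD14+CD16+ | intermediate | intermediate | none | none |
| CD14+CD16++ | none | intermediate | non-classic | non-classic |

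Under distinct levels, the printed definitions count CD14++CD16+ and CD14+CD16++ cells in neither subset. Under the inclusive reading, both go to intermediate, and every cell meeting the non-classic definition is counted as intermediate as well. On neither reading do the printed definitions yield separate subsets that match the names.

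The number of unassigned combinations is not itself evidence for the exchange. With distinct levels it is 3 of 6 before and 3 of 6 after.

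**Step 3: extent.** Two of the three monocyte components are affected. If percentage and absolute number apply to the whole list in section 3, that is 2 subsets x 2 units x 3 follow-up visits = 12 changes from baseline per participant. The size of the error in any of them cannot be computed, because the protocol gives no cell frequencies.

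**The case against.** The strongest objection is that the protocol never says what the monocyte names mean. It cites no nomenclature, and the labels fit the CD16 order. On that view the printed definitions are a local convention, and calling them wrong imports an outside standard. Part of this stands: the exact correction rests on ordinary usage, so it should be confirmed with the laboratory. It does not remove the problem that a subset called intermediate is lowest of the three on CD14, or that one reading of the symbols nests non-classic inside intermediate.

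A second objection is that the laboratory manual may carry the gating actually used. It may. But section 8.2.3 ties the manual to tests as defined in Appendix 2, and Table 3 of that appendix prints the same symbols. If the laboratory departs from them, the protocol misdescribes its endpoint and still needs correcting.

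Agreement between sections 8.3 and 10.2 is weak support for the text. In Table 3 the effector memory T-cell phenotype is printed as CD27-CD45RA+, identical to the TEMRA phenotype in the same table, whereas section 8.3 gives CD27-CD45RA- for effector memory. The marker strings were evidently not closely checked.

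Three stronger readings are tempting and are not supported:

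- A reader might infer that the two subsets have been miscounted in every participant. The documents do not show which gating was run.
- A reader might infer that both markers are crossed. The CD16 symbols are in order; only CD14 is at issue.
- A reader might infer that cells are certainly dropped from all subsets. That needs one plus and two pluses to be exclusive levels. Elsewhere in section 8.3 a single plus simply marks positivity, and on that reading the fault is overlap.

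**Conclusion.** The point holds in a limited form. The CD14 symbols of the intermediate and non-classic subsets appear transposed in sections 8.3 and 10.2. If the definitions are applied as printed, those two components of the secondary immune-profile endpoint would not describe the named subsets at baseline or at weeks 48, 96 and 144.

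This rests on two assumptions: that the subset names carry their ordinary meaning, and, for any effect on data, that the laboratory followed the printed text. The first is well supported by the broken CD14 order; the second cannot be judged from the protocol.

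The consequence is confined to two components of one secondary endpoint that covers many other cell populations. The classic subset, the primary PhenoAge comparison and the sample size are untouched. The correction is worth making because it is nearly free and the alternative is a mislabelled result.

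**What to change.** In section 8.3 and in Table 3 of section 10.2, exchange the CD14 symbols so that the definitions read classic CD14++CD16-, intermediate CD14++CD16+ and non-classic CD14+CD16++. Before issuing the change, confirm it against the laboratory's actual gating template and laboratory manual.

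State that the three subsets are mutually exclusive. This is needed because, on the inclusive reading of a single plus, CD14++CD16++ cells would still fall in two subsets after the exchange. Give the cut-offs, or refer to the template that holds them, and say how monocytes outside all three subsets are handled.

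Apply one template to baseline and to weeks 48, 96 and 144. Where samples have already been acquired under the printed definitions, re-gate the acquired files if they were kept; the protocol does not say whether they are.

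The cost is a two-line correction in two places and some software re-analysis. No new sample or assay is needed.
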